**5. Test method and course of treatment**

5.1 Test method:

The trial is a randomized, controlled, open-label, multicenter clinical study. Qualified subjects after screening will be randomly divided into 3 groups (Groups A, B and C) using centre-stratified block-permuted randomization, with 30 patients in each group and 90 patients in total:

5.2 Drug usage:

1. In MTX therapy, the initial dose is 10mg/ week, which will gradually be increased to 15 mg/ week (in Week 4);
2. At the same time, 25mg of RhTNFR:Fc (trade name: Yisaipu) will be injected subcutaneously each time, twice a week for treatment.
3. The subjects will be treated with the combined use of MTX according to the above regimen until Week 52, and endpoint evaluation will be conducted. The dose of MTX could be reduced for safety reasons. If the subjects could not tolerate the dose reduction, the event could be recorded as an adverse event. After reduction, the dose could be restored to the prescribed dosage when the investigator thinks it is appropriate.
4. Diagram of drug usage:

Group A:

(RhTNFR:Fc + MTX group), 52 weeks; n=30

Group B:

"MTX monotherapy"; n=30

(RhTNFR:Fc + MTX group)

Group C:

"MTX monotherapy"; n=30

Baseline

52 weeks

24 weeks

4 weeks

12 weeks

36 weeks

MTX dose increase stage: MTX will be increased from 10 mg/ week to 15 mg/ week

Note: Folic acid at 5 mg/ week will be given on the Day 2 of MTX administration in the trial.

5.3 Criteria for drug withdrawal:

If one of the following conditions occurs, the investigator may consider drug discontinuation for observation:

1. A serious adverse event occurs, and it has certain relationship with the investigational drug;
2. An adverse drug reaction occurs, and effective remission cannot be achieved after symptomatic treatment;
3. Laboratory tests: transaminase > 3 times the normal value or WBC < 3×109 /L, or PLT < 100×109 /L;
4. The subject has other diseases, and the investigational drug may aggravate the condition.

5.4 Withdrawal from the trial:

For the patients who withdraw during the trial, the investigator must record the reason and date of withdrawal in detail. Patients who may withdraw during the trial can be divided into the following categories:

- 1. Patients found to fail to meet the inclusion/exclusion criteria during the trial;
  2. Treatment discontinuation > 4 weeks during the medication due to adverse drug reaction or other reasons (e.g. the treatment has to be discontinued due to occurrence of other disease, migration to other places and loss to follow-up); or within 24 weeks, the accumulated duration of drug discontinuation has exceeded 8 weeks;
  3. Subjects who withdraw the drug by themselves and give up continuing the trial;
  4. Due to serious adverse drug reaction, the drug must be withdrawn in advance.
  5. Those with poor compliance and failing to take the drug according to the schedule or design;
  6. Those with concurrent occurrence of other serious diseases and the investigator considers inappropriate to continue the medication;
  7. Those failing to complete all the examination items as required and thus not evaluable.

5.5 Trial assessments:

The screening visit will be completed within 3 weeks (21 days) before the first administration of the investigational drug. The baseline visit and randomization will be conducted on the day of the first administration, and informal visits will be conducted every 4 weeks to understand the medication and adverse events of the subjects. Formal visits will be conducted every 12 weeks, and the visit results will be recorded. The endpoint visits will be conducted at week 52. In addition to the baseline, the time window for each visit is ±7 days (based on the baseline).

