4) Definitely unrelated: the reaction occurs not following a reasonable temporal sequence from administration of the drug and falls into the known reaction types of other drugs than the investigational drug; the reaction could also be caused by the subject’s clinical state or other therapeutic methods, and the disease condition improves or symptoms of the reaction disappears after withdrawal of other therapeutic methods but appears again after resumption of other therapeutic methods.

5) Not evaluable: the reaction occurs not following a definite temporal sequence from administration of the drug and resembles the known reaction types of the drug, but it could also be caused by other drugs used at the same time.

The 1), 2) and 5) of the above 5 items are recorded as adverse reactions (ARs) of the drug.

Incidence of ARs: Number of patients experiencing ARs / Total number of patients × 100%.

8.5 Assessment of infection and other serious adverse events (SAEs):

Close attention should be paid to the occurrence of infection during observation and make statistics accordingly; in case of any serious adverse reaction (SAR) (e.g., serious infection and serious local reaction), the drug should be withdrawn immediately, the sponsor contacted as soon as possible and symptomatic treatment given promptly. If it is a mild or moderate AR, symptomatic treatment may be given first for observation; if the symptom is still not alleviated, the drug should be withdrawn and the changes in the disease condition should continue to be observed.

Re-examination should be performed immediately if the laboratory findings are slightly abnormal, e.g., elevated transaminase level; if the abnormalities persist, symptomatic treatment should be given for observation, and observation of changes in the disease conditions continued. The drug should be withdrawn immediately if the abnormalities continue to worsen or serious abnormalities occur.

8.6 Assessment of SAEs:

SAE is defined as any AE that occurs at any dose of the investigational drug or at any time during observation, including those that are immediately life-threatening, necessitate hospitalization or prolonged hospitalization, lead to disability, or cause congenital malformation or permanent loss of function.

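### Sections 5.3 and 8.5 conflict on stopping the drug: for drug-related serious events and for reactions not relieved by treatment, one leaves stopping to discretion and the other directs it.

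*Protocol*

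**What the plan says.** Section 5.3 of the Protocol lists four conditions under one permissive lead-in: "the investigator may consider drug discontinuation for observation". Three of them matter here:

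- Item 1: "A serious adverse event occurs, and it has certain relationship with the investigational drug".
- Item 2: "An adverse drug reaction occurs, and effective remission cannot be achieved after symptomatic treatment".
- Item 3: "Laboratory tests: transaminase > 3 times the normal value", or white cells below 3×10⁹/L, or platelets below 100×10⁹/L.

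Section 8.5 covers the same ground in directive terms. For a serious adverse reaction, "the drug should be withdrawn immediately, the sponsor contacted as soon as possible and symptomatic treatment given promptly". For a mild or moderate reaction, symptomatic treatment may be tried first, and if it brings no relief the drug is to be withdrawn. For laboratory findings there is a graded response: repeat the test if slightly abnormal, then treat and observe if it persists. Beyond that, "The drug should be withdrawn immediately if the abnormalities continue to worsen or serious abnormalities occur".

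Section 5.4 bears on the point in two places. Item 4 reads "Due to serious adverse drug reaction, the drug must be withdrawn in advance", within a list introduced by "Patients who may withdraw during the trial can be divided into the following categories". Item 2 makes an interruption a withdrawal category once it exceeds 4 weeks, or once accumulated time off drug exceeds 8 weeks within 24 weeks.

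**The concern.** A stopping rule should give one answer for one event. Here an investigator who consults the section on drug withdrawal finds permission to stop, and one who consults the safety section finds an instruction to stop. Both can claim to have followed the protocol.

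Patient safety is the first thing at stake, because treatment could continue under one section where the other directs that it cease. There is also a route into the analysis. A stop can lead to withdrawal under 5.4, withdrawals for adverse events are reported under 9.2, and 9.1 fills unobserved values by LOCF. The primary endpoint is the Sharp score, and the flow chart schedules hand films only at baseline, Week 24 and Week 52, with no early-termination visit. A patient withdrawn after Week 24 could therefore have the Week 24 film carried to Week 52. Treatment is open label, so discretion under 5.3 is exercised with the allocation known.

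**Working it through.** The protocol gives no figure to reproduce, and the point depends on no power or sample-size input. The check is a comparison of the rules, event by event.

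| Event | 5.3 | 8.5 | 5.4 | Result |
|---|---|---|---|---|
| Serious event related to the drug | Optional (item 1) | Withdraw immediately | Item 4 says *must*, but as a withdrawal category | Conflict between 5.3 and 8.5 |
| Reaction not relieved by symptomatic treatment | Optional (item 2) | Withdraw (mild or moderate reactions) | No matching rule | Conflict between 5.3 and 8.5 |
| Laboratory abnormality | Optional at numeric limits (item 3) | Withdraw immediately if worsening or serious; no limits given | No matching rule | Overlap |

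**Serious related event.** Section 5.3 speaks of a serious adverse event and 8.5 of a serious adverse reaction, so the two triggers need to be matched. Section 8.4 counts an event as an adverse reaction if it is definitely related, possibly related or not evaluable. A serious event that is related to the drug is therefore a serious adverse reaction, whether 5.3 means a definite relationship or only some relationship. The same patient meets both rules: 5.3 permits a stop and 8.5 directs one at once.

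**Unrelieved reaction.** Item 2 of 5.3 has no severity limit, so it includes the mild and moderate reactions for which 8.5 directs withdrawal after symptomatic treatment fails. For those reactions the trigger is essentially the same and the force differs.

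**Laboratory values.** Section 8.5 does not define a serious abnormality and does not refer to the limits in 5.3. Its own example of a slight abnormality is a raised transaminase, with no level given. Two cases follow:

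- A value past a 5.3 limit that is still worsening meets both rules, optional in one and immediate withdrawal in the other.
- A value past a 5.3 limit that is stable meets 8.5 only if it is judged serious, and the protocol does not say whether crossing the limit makes it so.

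**Precedence.** Neither section refers to the other. No text says that one prevails or that 5.3 applies only to events outside 8.5.

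**The case against.** The strongest reply is that the sections describe successive steps. On this reading, 5.3 is a pause for observation, item 2 of 5.4 says when a pause becomes a trial withdrawal, and 8.5 is the permanent stop. Part of this stands: item 2 does connect interruption to withdrawal, so 5.3 and 5.4 are largely compatible. It does not reconcile 5.3 with 8.5. The heading of 5.3 itself concerns drug withdrawal, the protocol never separates a pause from a withdrawal, and even a pause is only optional in 5.3 where 8.5 directs a stop.

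Several stronger readings are tempting, and the documents do not support them:

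- *Section 5.4 makes stopping mandatory for all three kinds of event.* It does not. Item 4 covers serious reactions only and stands in a list that classifies patients who withdraw, so it can be read as a reason for withdrawal. It is weaker support than 8.5, and the conflict does not need it.
- *The laboratory rules contradict each other outright.* They do so only where a value past a 5.3 limit is also worsening or judged serious. Otherwise both can be followed, and the defect is an undefined term.
- *Inconsistent stops would use up the loss allowance.* The plan enrols 30 per group for 25 needed, an allowance of 30 − 25 = 5. But the documents give no rate for these events. A short interruption is not a withdrawal under item 2 of 5.4. Section 9.1 also keeps in the ITT set, by LOCF, any stopped patient who has had one dose and one post-treatment effectiveness evaluation.
- *Site differences would bias the comparison between arms.* Randomization is stratified by centre in permuted blocks, so a site that follows one section throughout applies it to all three arms. What remains is open-label discretion that varies with the known treatment, which is possible but not shown.

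**Conclusion.** The conflict between 5.3 and 8.5 is established from the text for drug-related serious events and for mild or moderate reactions not relieved by symptomatic treatment. For laboratory abnormalities it is established as an overlap, created by the missing link between the 5.3 limits and the term used in 8.5.

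The consequence is mainly one of patient safety. The effect on the adverse-event dropout rate in 9.2 and on the number of values filled by LOCF is real in direction, since both can depend on which section is followed. Its size cannot be stated, because the documents give no rate of serious reactions, unrelieved reactions or laboratory events, and no indication of how sites would read the two sections.

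The conclusion assumes that the shown text is the whole of the stopping guidance. It does not depend on any view of which rule is clinically right, and none is offered.

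**What to change.** Reconcile 5.3, 8.5 and item 4 of 5.4 so that each trigger has one rule, stated once and referred to elsewhere. For a related serious event, an unrelieved reaction and each laboratory limit, the text should say whether stopping is optional or mandatory, and whether it is an interruption or a withdrawal. The wording should be consistent with the 4-week and 8-week interruption limits in item 2 of 5.4. Section 8.5 should either tie its term for serious abnormalities to the limits in 5.3 or state that the two differ and how.

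The sponsor and investigators decide the clinical content. The cost is a wording amendment and a letter to the seven sites, with no added procedures, visits or patients.

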5.6 Standardized sequence of visit evaluation

1. Health assessment of subjects (HAQ)
2. Measurement of subjects' own assessment (VAS for pain and VAS for overall assessment of disease activity)
3. Therapists or joint assessors:
   1. Counting of affected joints
   2. Overall evaluation of disease activity VAS and safety (adverse events, vital signs, concomitant medication, laboratory data review).
4. The therapists prescribe tests and special examinations, guiding the subjects to draw blood and receive X-ray and other laboratory examinations.

5.7 Assessment personnel

1. Joint assessors:

Rheumatologists or experienced arthritis assessors who have no right to know about other data information of the subjects. At each visit, each subject will be evaluated by the same joint evaluator.

1. Principal Investigator:

Rheumatologists who have the right to know about other data information of the subjects, and could make all treatment decisions according to the clinical treatment response and laboratory indexes of the subjects.

**6. Efficacy observation indicators:**

6.1 Clinical observation indicators and assessments:

6.1.1 Rest pain:

Using 100 mm visual analog scale, each subject indicates the degree of pain;

**
[figure not shown]
**

**10**

**0**

**20**

**30**

**40**

**50**

**60**

**70**

**80**

**90**

**100 mm**

6.1.2 Duration of morning stiffness (min):

Each subject records the time from the occurrence to the disappearance of joint stiffness when waking up in the morning;

6.1.3 Joint swelling:

The swollen joint count will be recorded (SJC, 66 joints counted)

6.1.4 Joint tenderness:

The tender joint count will be recorded (TJC, 68 joints counted)

6.1.5 Health Assessment Questionnaire (HAQ):

Before and after treatment, each subject assesses his/her own ability of daily living, including 20 indicators, such as dressing, standing, eating and drinking, walking, hygiene and grasping. The assessment includes 4 levels: 0= not difficult; 1= slightly difficult; 2=very difficult; 3= incapable. See the attachments for details.

6.1.6 Subject's assessment on the current disease status:

The 100 mm visual analog scale is used to assess the comprehensive disease condition before and after medication. The following way can be used for asking: “Considering all factors of arthritis that affect you, please indicate your current status in the scale with ‘X’”. The following degree classification can be used in combination for assessing the disease degree.

**
[figure not shown]
**

**10**

**0**

**20**

**30**

**40**

**50**

**60**

**70**

**80**

**90**

**100 mm**

6.1.7 Doctor's assessment on the current disease status:

The 100 mm visual analog scale is used to assess the comprehensive disease condition before and after medication. The method of assessment is the same as above.

6.2. Conventional laboratory indicators:

The blood routine examination, biochemical examination, erythrocyte sedimentation rate test (ESR, Wechsler method, normal values: ≤ 15 mm/h for males, ≤ 20 mm/h for females) and C-reactive protein test (CRP, quantitative method) will be conducted before treatment and at week 12, 24, 36 and 52 after treatment.

The urine routine examination will be conducted before treatment and at week 12, 24, 36 and 52 after treatment.

The rheumatoid factor (RF) examination and ANA will be conducted before treatment, and at 24 and 52 weeks after treatment.

The anti-CCP antibody test (2nd generation) will be conducted before treatment.

6.3. Safety observation indicators:

PPD, HbsAg antibody, HCV-Ab and HCV antibody were checked before enrollment. The laboratory indexes to be monitored in the trial included: blood routine, urine routine, liver and kidney function, ANA and chest radiography.

6.4. Imaging observation indicators:

The examinations for both hands include X-ray and MRI of wrist joints, and other parts will be examined if necessary. The Sharp score is used to evaluate the affected joints.

**7. Efficacy evaluation:**

7.1 Primary endpoints:

Improvement in Sharp score of X-ray of affected joints.

7.2 Secondary endpoints:

1. Proportion of subjects reaching ACR20, ACR50 and ACR70: ACR50 and ACR70 are defined as 50% and 70% improvement respectively using the same criteria as ACR20.
2. Average changes of ACR core parameters relative to the baseline level
3. Average change of HAQ score from baseline to Week 52
4. Time for each treatment group to reach ACR20, 50 and 70
5. The proportion of subjects with low disease activity at each visit
6. The proportion of subjects achieving disease remission at each visit
7. MRI changes (joint space narrowing and bone erosion)

7.2.1 The response definition of ACR20 is: there is 20% improvement in the number of swollen and tender joints (28), as well as 20 % improvement in at least 3 of the 5 following items:

1. The VAS score of pain assessed by the subject;
2. The VAS score of overall disease condition assessed by the subject;
3. The VAS score of overall disease condition assessed by investigator;
4. Health Assessment Questionnaire (HAQ);
5. Acute phase reactant (ESR or CRP).

7.2.2 DAS28:

[figure not shown]
(28 joints)

The disease activity score of 28 joints will be calculated as follows:

DAS28 = 0.56 × + 0.28 × + 0.7 × ln(ESR) + 0.014 × GH

TJC: Tender joint count, SJC: Swollen joint count, ESR: erythrocyte sedimentation rate (in mm/h), GH: general health status expressed in the 100 mm VAS.

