**Efficacy Observation Indicators:**

Before treatment, 12, 24, 36 and 52 weeks after treatment, the rest pain, morning stiffness duration, swollen joint count and tender joint count , and health assessment (HAQ), subject's assessment of disease, and doctor's assessment of illness will be evaluated.

CRP and ESR will be evaluated before treatment and at 12, 24, 36 and 52 weeks after treatment.

X-ray changes of both wrists (Sharp score) before treatment and 24 and 52 weeks after treatment.

If necessary, MRI before treatment and at Week 52 (15 patients in Group A and 15 patients in Group C respectively; 30 patients in total).

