**9. Statistical methods:**

9.1 Selection of statistical analysis data:

Intent-to-treat (ITT): all subjects eligible and enrolled after screening and having taken at least one dose of the drug and received at least one post-treatment effectiveness evaluation; LOCF (last observation carry-forward) will be adopted for those subject’s data not observed during the whole treatment course, that is, estimating the missing values of important indicators using the closest observed data. The ITT analysis will be used in this trial.

Safety population: it includes all subjects having taken at least one dose of the drug and received at least one post-treatment safety evaluation.

9.2 Statistics Analysis Plan:

Statistical analysis will be carried out using the SAS statistical analysis software. A sample size of 90 patients was estimated for the open label period with the assumption that mean mTSS CRF was -0.5±1.0 in the MTX plus rhTNFR:Fc group, and 2.5±5.0 in the MTX group at week 52. A sample size of 25 patients per treatment group was calculated to be necessary for more than 80% power to reject the null hypothesis of no difference among the treatment groups with an α of 0•05. Assuming loss of patients, the study required a minimum of 30 patients in each group. Two-sided test will be used for all statistical tests, and the difference tested will be considered as statistically significant if the P value is equal to or less than 0.05. Measurement data will be statistically described using mean±SD (standard deviation). Paired t-test will be used for intra-group differences before and after the treatment. Enumeration data will be statistically described using frequency (constituent ratio).

Dropout analysis: Calculate the dropout rates and the rates of dropout due to AE.

Efficacy analysis: The paired t test or nonparametric test or chi-square test will be used to evaluate the efficacy indexes.

Safety analysis: Calculate the incidence rate of adverse events and tabulate the AEs occurring during the trial, normal/abnormal changes in laboratory findings before and after the trial, as well as relationships of abnormal changes with the investigational drug

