Attachment I: Trial Flow Chart

Attachment II: Health Assessment Questionnaire (HAQ)

Attachment III: Sharp Score Criteria

Attachment IV: Wrist X-ray Staging Criteria for Rheumatoid Arthritis (ACR)

Attachment V: Table of Swollen and Tender Joint Count

**Attachment I:**

**Trial Flow Chart**

| **Work Contents** | **Baseline Period** | **Treatment Period** | | | |
| --- | --- | --- | --- | --- | --- |
| **D-7~0** | **12W±7d** | **24W±7d** | **36W±7d** | **52W±7d** |
| **Informed consent** | **√** |  |  |  |  |
| **Inclusion criteria** | **√** |  |  |  |  |
| **Exclusion criteria** | **√** |  |  |  |  |
| **Medical history collection** | **√** |  |  |  |  |
| **Vital signs** | **√** | **√** | **√** | **√** | **√** |
| **Physical examination** | **√** | **√** | **√** | **√** | **√** |
| **HBs-Ag/HCV-Ab** | **√** |  |  |  |  |
| **Tuberculin test (PPD)** | **√** |  |  |  |  |
| **Chest X ray** | **√** |  |  |  | **√** |
| **Disease status assessment** | **√** | **√** | **√** | **√** | **√** |
| **Routine blood test** | **√** | **√** | **√** | **√** | **√** |
| **Urinalysis** | **√** | **√** | **√** | **√** | **√** |
| **Blood chemistry test** | **√** | **√** | **√** | **√** | **√** |
| **Erythrocyte sedimentation rate (ESR)** | **√** | **√** | **√** | **√** | **√** |
| **C-reactive protein (CRP)** | **√** | **√** | **√** | **√** | **√** |
| **Rheumatoid factor** | **√** |  | **√** |  | **√** |
| **Anti-CCP (2nd Generation) antibody** | **√** |  |  |  |  |
| **Antinuclear antibody (ANA)** | **√** |  | **√** |  | **√** |
| **ECG** | **√** | **√** | **√** | **√** | **√** |
| **X-ray of both hands (including wrist joint)** | **√** |  | **√** |  | **√** |
| **MRI** | **√** |  |  |  | **√** |
| **Medication administration record** |  | **√** | **√** | **√** | **√** |
| **Documentation of concomitant medications** | **√** | **√** | **√** | **√** | **√** |
| **Adverse event evaluation** |  | **√** | **√** | **√** | **√** |
| **Clinical efficacy evaluation** |  | **√** | **√** | **√** | **√** |

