**Attachment III:**

**Sharp Score Criteria**

**Joint Erosion Score (ES)**

The simple scoring method is: The joint is divided into 4 equal parts, and 1 point is given if there is erosion in each part. If there is an intersection part, it is scored according to one fifth of the eroded area of the joint, with one point for every one fifth.

[figure not shown]

With the erosion scores being 0-5, the judgment criteria are as follows:

0 = no erosion;

1 = 1 quarter joint part is eroded alone, or the eroded area of the joint is ≤ 20%;

2 = 2 quarter joint parts are eroded respectively, or 20% < joint eroded area ≤ 40%;

3＝3 quarter joint parts are eroded respectively, or 40% < joint eroded area ≤ 60%；

4＝4 quarter joint parts are eroded respectively, or 60% < joint eroded area ≤ 80%；

5 = the joint is completely destroyed.

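### The primary endpoint in 7.1 is not tied to the Week 52 mTSS change on which the trial is sized, and the protocol's sections disagree on which joints are scored

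*Protocol*

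**What the plan says.** The whole definition of the primary endpoint, in Protocol 7.1, is "Improvement in Sharp score of X-ray of affected joints". In the list of secondary endpoints that follows, the HAQ item does state a baseline and Week 52.

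The joints to be filmed and scored are described in three other places:

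- Summary, Efficacy Observation Indicators: "X-ray changes of both wrists (Sharp score) before treatment and 24 and 52 weeks after treatment".
- Section 6.4: "The examinations for both hands include X-ray and MRI of wrist joints, and other parts will be examined if necessary", followed by "The Sharp score is used to evaluate the affected joints".
- Attachment I, flow chart: "X-ray of both hands (including wrist joint"), ticked at baseline, Week 24 and Week 52.

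Section 9.2 sizes the trial on the assumption that "mean mTSS CRF was -0.5±1.0 in the MTX plus rhTNFR:Fc group, and 2.5±5.0 in the MTX group at week 52". Neither mTSS nor CRF is defined, and mTSS appears nowhere else in the protocol.

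On timing, 5.2 and 5.5 place the endpoint evaluation and the endpoint visit at Week 52, and 9.2 assumes Week 52. The Summary's Efficacy Evaluation lists Weeks 24 and 52 without ranking them.

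Attachment III grades a single joint (erosion 0 to 5, narrowing 0 to 4). Its text gives no joint list and no rule for adding joints up. The top erosion grade reads "5 = the joint is completely destroyed".

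**The concern.** A primary endpoint must be one variable, measured the same way in every patient. A score over two wrists, a score over both hands and wrists, and a score over whichever joints count as affected are three different variables with different ranges. The sections do not settle which is meant, and 6.4 lets the joint set grow for some patients and not others. The trial is open-label, so whoever decides that another part is needed may know the treatment.

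The word 'affected' adds a second problem. If it means affected at baseline, a new erosion in a clean joint never enters the score, although preventing joint destruction is part of the rationale in Section 1. If it means affected at the time of the film, the list of scored joints can change between visits.

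Finally, the sizing assumption in 9.2 concerns a named score at a named visit. Unless 7.1 names the same score and visit, a reader cannot confirm that the planned 25 per group applies to the endpoint that will be tested.

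**Working it through.** **1. The sample size from the plan's own inputs.** From 9.2: means -0.5 and 2.5, so difference 3.0; SDs 1.0 and 5.0; two-sided α 0.05; 25 per group for more than 80% power; 30 per group after loss.

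- Standard error at n = 25: √(1.0²/25 + 5.0²/25) = √(26/25) = 1.020.
- Noncentrality: 3.0 / 1.020 = 2.94.
- Unequal-variance (Welch) t-test, about 25.9 degrees of freedom, critical value 2.056: power 80.8%.
- At n = 24 the same calculation gives 79.1%, so 25 is the smallest size above 80%.
- Loss: 1 − 25/30 = 16.7% implied (no rate is stated). With all 30 evaluable, power is 87.7%.

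The stated 25 reproduces. Any difficulty lies in the variable and not in the arithmetic.

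**2. The endpoint across sections.**

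| Place | Region or joints | Score | Time |
|---|---|---|---|
| 7.1 | affected joints, undefined | Sharp | not given |
| Summary, Efficacy Observation Indicators | both wrists | Sharp | baseline, Weeks 24 and 52 |
| 6.4 | hands/wrists, other parts if needed; affected joints scored | Sharp | not given |
| Attachment I | both hands with wrists (films) | none named | baseline, Weeks 24 and 52 |
| 9.2 | not given | mTSS, undefined | Week 52 |
| Attachment III | no joint list in the text | per-joint erosion and narrowing | not applicable |

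No two of the first four rows give the same joint set. The only row that names the sizing score gives no joints. So the link from 7.1 to 9.2 is never stated, and more than one joint set complies with the protocol.

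**3. Time point.** 7.1 is silent. Sections 5.2, 5.5 and 9.2 all point to Week 52. Only the Summary leaves Weeks 24 and 52 unranked.

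**4. Grades in Attachment III.** By area, erosion grade 4 covers more than 60% up to 80%, and grade 5 is complete destruction. A joint eroded above 80% but short of that has no area band of its own. The quarter rule would give 4 if all four quarters are eroded, while the rule of one point per fifth could be read as 5. Narrowing of exactly 60% fits both grade 2 and grade 3.

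**The case against.** **'Affected' need not exclude anything.** Neither 7.1 nor 6.4 says affected at baseline. A joint first eroded at Week 52 is affected at Week 52. Because Attachment III gives unaffected joints zero, summing the affected joints at each film equals summing all joints of the same region. This stands against any claim that new erosions are excluded: a reader might infer it, but the text does not say it. It does not remedy the missing definition, and it does not help where the region itself differs between patients.

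**Power might seem to fall.** A reader might suppose that 10%, 30% or 50% of MTX progression (2.5 points) lies in unscored joints, so that the difference becomes 3.0 − 2.5 × share, that is 2.75, 2.25 or 1.75. These shares are assumptions that are not in the documents. Welch power at n = 25, with the combination group unchanged, then depends on what happens to the MTX SD:

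| MTX SD | 10% | 30% | 50% |
|---|---|---|---|
| held at 5.0 | 74% | 57% | 38% |
| shrinks with the mean | 82% | 85% | 88% |
| variance shrinks with the mean | 78% | 71% | 63% |

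Against 80.8%, power can fall or rise. The documents support neither a size nor a direction, so no loss of power should be claimed.

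**Week 52 can be inferred, and detail can sit elsewhere.** Both are fair. Week 52 follows from three sections, and a full joint list or maximum score could be left to a SAP or reading manual that is not shown. But a later document would still face protocol sections that disagree on the region, and that disagreement has to be resolved in the protocol.

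**Conclusion.** The point holds as a defect in the definition of the primary endpoint. Section 7.1 does not name the Week 52 mTSS change used in 9.2, 'affected' is undefined, and the sections give different joint regions, one of them open to discretion. This goes beyond missing detail, because following the text literally permits different joint sets in different patients.

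It would go too far to say that the endpoint is a different quantity from the mTSS change. With mTSS undefined, the documents show neither that the two agree nor that they differ. It would also go too far to say that no time point exists, or that a joint eroded above 80% cannot be scored; the first is an omission in 7.1 and the second an ambiguity.

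The consequence cannot be expressed in power. The sample size of 25, or 30 with allowance for loss, reproduces and is unchanged, provided that the sizing assumption refers to the score and joint set finally fixed. The grading overlaps in Attachment III are minor.

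**What to change.** Rewrite 7.1 along these lines: the primary endpoint is the change from baseline to Week 52 in the total modified Sharp score (erosion plus joint space narrowing), summed over one fixed set of joints of both hands and wrists, the same in every patient and at every film, whether or not a joint is affected at baseline. The Week 24 change is secondary.

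Then:

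- Align the Summary's Efficacy Observation Indicators, 6.4 and the flow chart with that joint set, so that any additional parts filmed under 6.4 do not enter the primary score.
- Define mTSS in 9.2 and state that the sizing assumption refers to this score at Week 52.
- As a minor point, make the Attachment III grades exhaustive and disjoint: place erosion above 80% but short of complete destruction consistently with the one-point-per-fifth rule, and put 60% narrowing in one grade only.

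The cost is protocol wording and perhaps the scoring of more joints per film. The hand films are already scheduled at baseline, Week 24 and Week 52, and no patients are added.
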